## Abstract

**Background:**

Williams syndrome (WS-OMIM 194050, orphaned number: Orpha 904) is a rare condition mostly associated with intellectual disability. People with Williams syndrome are 8 times more likely to have anxiety disorders than the general population. Therapeutic solutions to treat the anxiety remain limited, particularly nonpharmacological therapy. However, cognitive behavioral therapy (CBT) has been found efficacious in managing anxiety disorders and can be used for people with intellectual disability.

**Objective:**

This paper describes a protocol to assess the efficiency of a CBT program based on digital support for people with Williams syndrome and anxiety based on a research methodology designed for rare diseases.

**Methods:**

We will recruit 5 individuals with Williams syndrome and anxiety. They will participate in 9 CBT sessions. Participants will perform daily self-assessments of anxiety using a digital app, which will allow for ecological and repeated evaluation of their anxiety. This digital app will provide support for each therapy session. Anxiety and quality of life will be externally assessed before and after the program and at a 3-month follow-up. This is a single-case intervention research design with multiple baselines implying repeated measures of judgment criteria. The present protocol ensures high internal validity and will help identify encouraging contributions for later clinical trials.

**Results:**

Participant recruitment and data collection began in September 2019, and we project that the study findings will be available for dissemination by spring 2023.

**Conclusions:**

This study will allow the assessment of the efficiency of a CBT program based on digital support to treat anxiety in people with Williams syndrome. Finally, the program could be used as an example of nonpharmacological therapy for rare diseases.

**Trial Registration:**

ClinicalTrials.gov ID: NCT03827525; https://clinicaltrials.gov/ct2/show/NCT03827525

**International Registered Report Identifier (IRRID):**

DERR1-10.2196/44393

## Introduction

Williams syndrome (WS) is a rare neurodevelopmental disorder caused by a 7q11.23 deletion encompassing about 25 genes on chromosome 7 [1]. The estimated prevalence is 1 in 7500 live births [2]. Most individuals present with intellectual disability and peculiarities in neuropsychological functioning. The cognitive profile is heterogeneous in terms of strengths and weaknesses and in global functioning [3]. Language skills are generally good, often with deficits in certain executive functions (especially inhibition) [4].

The prevalence of anxiety disorders in WS is high, varying from 16% to 82% [5]. With an anxiety rate 8 times higher than in the general population and 4 times higher than in other individuals with intellectual disability [6], it is the most prevalent mental health problem for individuals with WS. The available drug treatments have been found effective in reducing the level of anxiety in individuals with WS. However, they have side effects [7]. Despite the consequences on quality of life (QoL), there is a lack of research on therapeutic protocols for anxiety for people with WS.

Cognitive behavioral therapy (CBT) belongs to a class of scientifically validated therapeutic interventions. It aims to modify dysfunctional ways of thinking, as well as behavioral patterns, to reduce psychological problems. CBT interventions for anxiety share a focus of changing dysfunctional beliefs and anxious anticipation by using different cognitive, behavioral, and emotional techniques [8]. A meta-analysis [9] showed that CBT provided greater clinical benefit than other forms of psychotherapy in treating several psychological disorders in individuals with intellectual disability. However, in the context of intellectual disability, the number of participants recruited in these studies remains low, and the methodologies used have numerous limitations (eg, no controlled manipulation of the treatment delivered, studies with only 1 patient [10-12], studies evaluating the impact of therapy during 1 week of hospitalization, studies do not allow for patient empowerment [13]). Many of the results tend to show that CBT is a promising therapy for treating the anxiety of patients with intellectual disability [14], but the few studies available and their methodological limitations make further research necessary [15].

A pilot study carried out in 2013 highlighted a mindfulness-based intervention for individuals with WS [13]. The practice of mindfulness is frequently used in CBT interventions. It teaches one to pay attention and to have moment-to-moment awareness [16]. This CBT treatment approach has been found efficacious in treating emotional disorders in individuals with WS. This pilot research took place in a 5-day institutional setting, and the long-term effects of the treatment were not evaluated. In addition, the application of treatment in a context of institutionalization raises the question of the generalization of the results and the autonomy of individuals with WS.

Another study was conducted in 2022, in which a group of 4 adults with WS were virtually delivered an adapted CBT intervention [17]. In this study, a CBT program was adapted for people with intellectual disability. Participants and caregivers in this study reported a high level of satisfaction and a reduction in their anxiety. This study provided support for the acceptability and feasibility of group-based CBT treatment for anxiety in WS. However, the sample size was small, and the methodology used did not have strong scientific reliability.

The objective of our study is to propose and discuss clinical interest in CBT with digital support for anxiety in people with WS, taking into account intellectual disability. Because of the rarity of WS, the single-case methodology seems appropriate. In addition, this methodology allows for analyzing the effects of the intervention at an individual level. The development of digital support will allow participants to perform the therapy exercises at home. This could be particularly interesting for people with intellectual disabilities who need to be assisted with the realization of a number of daily tasks. The objective of the digital support is to empower them. Furthermore, this application makes it possible for the patient to evaluate himself or herself from home on a daily basis, allowing an ecological repeated assessment. We hypothesize that patients with WS will be able to engage in an adapted CBT protocol. We hypothesize that individuals’ anxiety will decrease over the course of therapy. We also hypothesize that other factors such as QoL will be improved with this therapy protocol.

## Methods

### Study Design

We will use a multiple baseline AB single-case experimental design across participants to evaluate the efficacy of the intervention. This method allows for manipulating the intervention in an experimentally controlled manner and testing causal relations among variables of interest in a small group of participants. The multiple baseline design is well-suited for interventions that are irreversible due to learning effects, and it enables testing of whether the improvement in mental health is due to therapy or random factors changing with time [18]. For this purpose, we will use a multiple baseline across subjects and across behaviors design, as our patients will complete a daily self-assessment of 6 items related to their emotions. We will recruit only 5 patients because WS is a rare disease and a minimum of 3 replications of the effect is recommended to increase the reliability of our findings [19]. For each participant, we will first obtain repeated measures during the baseline phase (A) when no treatment is provided. Patients will be assigned to different lengths of the baseline phase to ensure at least 3 replications of the treatment effect [20]. The possible duration of the baseline phase ranges from 14 days to 30 days before treatment onset, as a minimum of 5 measurement points is required [21]. These repeated measures during the baseline phase serve as control conditions to evaluate what changes can be expected without the treatment [9,22]. The duration of the baseline will be randomly assigned by the experimenter. Following that, repeated measures are obtained during a 9-week treatment phase (B) and during 3 months after the treatment to ensure that our measures did not return to the baseline level after the treatment has been withdrawn. Patients will also complete a range of nomothetic outcome measures 3 times: (1) baseline, (2) intervention, and (3) follow-up termination.

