### Participants

We will recruit 5 participants for this study. The inclusion criteria are age >18 years, molecular confirmation of WS, sufficient level of language assessed by a score >7 on the Clinical Evaluation of Language Fundamentals 4 test [23], and complaints of anxiety. The complaints of anxiety can be expressed by the individual or the individual’s representative. For the inclusion criteria in this study, we chose to evaluate this complaint with the following Likert scale completed by the participant: “This week I have been anxious” or “This week the individual has been anxious.” To be included in the protocol, the participant will need to score at least 1 on this self-rated Likert scale. We chose to include people with low anxiety as well as high anxiety, even if an anxiety disorder is not characterized, because anxiety is generally underestimated in WS, with one longitudinal study finding co-occurring anxiety in approximately 82% of patients with WS [24].

Exclusion criteria are uncorrected visual disturbance, uncorrected deafness, or being already treated for anxiety. Because of the intellectual disability, individuals with WS will be accompanied by a caregiver during visits requiring signing consent or a hetero-evaluation.

Individuals will be recruited from patient associations and among individuals followed in the medical genetics department of Montpellier University Hospital. Interested individuals will receive information about the study, first with a letter; then, they will be in contact with a doctor involved in the study to ask questions. Because of the rarity of WS, individuals recruited could live far from the hospital where the study is taking place. Financial support for travel costs will be offered to each individual taking part in this study. Individuals with WS who wish to be involved and a legal representative will sign written informed consent; then, the individual will be prescreened for inclusion and exclusion criteria.

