### Procedures

#### Baseline

We will recruit 5 individuals with WS. Each participant will have a different length of the baseline period (A). The participants will be allocated to a baseline lasting from 2 weeks to 5 weeks. The baseline phase will begin at the same time for each participant. This multiple baseline design allows for the multiple assessments to serve as control conditions to evaluate what changes can be expected without the treatment [22]. During this baseline period, no therapeutic intervention will take place. The participants will continue their daily life without changing their habits. They will complete a daily self-assessment of 6 items related to their emotions.

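### The baseline maximum is 30 days in one section and 5 weeks in another, and no minimum gap between treatment onsets is stated, so three well-separated replications are not ensured.

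*Protocol article*

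**What the plan says.** The Protocol article describes a multiple-baseline AB design across participants, with no control arm. Participants: "We will recruit 5 participants for this study".

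The length of the baseline phase is given twice:

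- Study Design: "The possible duration of the baseline phase ranges from 14 days to 30 days before treatment onset".
- Procedures, Baseline: "The participants will be allocated to a baseline lasting from 2 weeks to 5 weeks".

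The rules for assigning lengths are:

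- Study Design: "Patients will be assigned to different lengths of the baseline phase to ensure at least 3 replications of the treatment effect", and "The duration of the baseline will be randomly assigned by the experimenter".
- Procedures, Baseline: each participant's length differs from the others', and "The baseline phase will begin at the same time for each participant".

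Study Design also justifies the lower limit: "as a minimum of 5 measurement points is required". Under Procedures, Intervention, the nine sessions are spaced one to two weeks apart. The article states no minimum difference between baseline lengths and no list of permitted lengths.

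**The concern.** The two sections give different upper limits for the same design parameter, so a reader cannot tell which set of lengths was randomised over.

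The parameter matters because the baselines are concurrent. A difference in baseline length is then exactly a difference in treatment onset, and the staggered onsets are what separates a therapy effect from something that happens to everyone at the same calendar time. Data Analysis describes visual analysis and Tau-U for each participant and target behaviour. It describes no between-participant comparison that would make up for a weak stagger.

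Two participants who start a day apart and then change over several weeks give nearly the same information about a shared event. Requiring the lengths to be different permits one-day gaps, so it does not by itself deliver the three replications that the article says it ensures.

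**Working it through.** **Inputs.** Five participants (Participants). Range 14-30 days (Study Design) or 2-5 weeks (Baseline). Lengths all different (both sections). Common start date (Baseline). Shortest session interval 7 days (Intervention).

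**Step 1: compare the ranges.** 2 × 7 = 14 days, which agrees with Study Design. 5 × 7 = 35 days, which does not agree with 30. The difference is 5 days. There are 30 − 14 + 1 = 17 possible whole-day lengths, or 35 − 14 + 1 = 22. With daily ratings, 14 days meets the 5-point minimum under either range.

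**Step 2: assumption.** The article does not say how lengths are drawn. Assume that every set of five different whole-day lengths is equally likely. There are C(17,5) = 6188 such sets, or C(22,5) = 26334.

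**Step 3: overall spread.** The mean first-to-last spread of 5 distinct values from N is 4(N + 1)/6.

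- 14-30: 4 × 18/6 = 12.0 days; mean gap between neighbours 12.0/4 = 3.0 days.
- 14-35: 4 × 23/6 = 15.3 days; mean gap 15.3/4 = 3.8 days.

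**Step 4: closest pair.** The share of sets in which all gaps are at least g is C(N − 4(g − 1), 5)/C(N, 5).

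| | 14-30 days | 14-35 days |
|---|---|---|
| All gaps ≥ 2 days | 1287/6188 = 20.8% | 8568/26334 = 32.5% |
| Some pair 1 day apart | 79.2% | 67.5% |
| All gaps ≥ 3 days | 126/6188 = 2.0% | 2002/26334 = 7.6% |

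**Step 5: three separated onsets.** This is closer to the article's own criterion of at least three replications. All sets were enumerated, counting those that contain three onsets mutually at least d days apart.

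| d | 14-30 days | 14-35 days |
|---|---|---|
| 3 days | 5863/6188 = 94.7% | 25704/26334 = 97.6% |
| 5 days | 3486/6188 = 56.3% | 20202/26334 = 76.7% |
| 7 days | 721/6188 = 11.7% | 10692/26334 = 40.6% |

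The 7-day row is the shortest session interval. The 3- and 5-day rows are illustrative, because the article sets no threshold.

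**Step 6: what even spacing could achieve.**

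- 14-30: (30 − 14)/4 = 4 days, for example 14, 18, 22, 26, 30.
- 14-35: (35 − 14)/4 = 5.25 days, for example 14, 19, 24, 29, 35, with gaps of 5, 5, 5 and 6 days.

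Whole-week steps do not fit five different lengths: 14-30 holds three (14, 21, 28) and 14-35 holds four (14, 21, 28, 35).

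**The case against.** The strongest reply is that a close pair does not defeat the criterion. Three replications are wanted from five participants, and one close pair still leaves four distinct onsets. If starts on consecutive days are merged, at least three separate onsets remain in 95% of draws (14-30) or 98% (14-35). If starts up to 2 days apart are merged, the shares are 71% and 85%. This stands. The 79% and 67% for a one-day pair show that near-simultaneous starts are likely, not that the criterion fails. The shortfall appears only at gaps of 5 days or more, and the article names no such threshold.

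The draw itself is also assumed. The full protocol may hold a fixed list of lengths, and an article commonly leaves that detail out. This too stands for the probabilities. It does not remove the contradiction between the two ranges.

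Even spacing gains only a little: gaps of 4 days, or 5 to 6 days, against means of 3.0 or 3.8 days. What it gains is certainty about the smallest gap.

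A reader might be tempted by four stronger readings, none of which the document supports:

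- *There is almost no stagger.* The mean first-to-last spread is 12.0 or 15.3 days.
- *Participants will often share the same length.* The Baseline section excludes ties: "Each participant will have a different length of the baseline period (A").
- *The undefined set of lengths spoils the planned inference.* Data Analysis plans visual analysis, Tau-U and the reliable change index; no randomisation test is planned.
- *The person making the draw knows the participants and could steer it.* The article says only that the experimenter assigns at random, and nothing about what that person knows.

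**Conclusion.** The contradiction is certain: the baseline maximum is 30 days in Study Design and 35 days in Baseline. It concerns the parameter that creates the trial's only between-participant control.

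The second part holds in a limited form. The stated rule does not ensure three well-separated onsets. They are very likely if 3 days counts as separate, roughly a coin toss to three in four at 5 days, and unlikely to uncertain at 7 days. This rests on equally likely whole-day lengths and on thresholds that the article does not give.

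Severity: should be fixed. It weakens the claim of ensured replication without invalidating the design.

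**What to change.** 1. Reconcile the two sections so that one baseline range is stated throughout. Which range is correct is for the investigators to confirm.
2. Within the confirmed range, fix five evenly spaced lengths (4-day gaps for 14-30, 5- to 6-day gaps for 14-35). Randomise only which participant receives which length, from a pre-generated list. If the full protocol already holds such a list, cite it.
3. Recruitment and data collection began in September 2019 (Results), so allocation may already be complete. In that case, report the actual lengths and onset gaps, state a minimum gap with its reason, and do not count onsets closer than that gap as separate replications. The gap should be chosen without reference to the outcome data.

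Cost: wording and a five-line list, with no extra participants or visits. The downsides are that only 5! = 120 assignments are then possible, and that the gaps remain shorter than one session interval. If allocation is complete, only the reconciliation and the reporting remain possible.

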#### Follow-up

After the 9 intervention sessions, individuals will be invited to continue to apply tools delivered during the intervention in their daily life. They will continue their daily self-assessment for 3 months after the intervention.

During the research (baseline, intervention, follow-up), the individual’s representative will complete daily evaluations.

Hetero-evaluations will be carried out during the inclusion visit (baseline), the visit at the start of the intervention (T1), the visit at the end of the intervention (T9), and the follow-up visit 3 months after the end of intervention (Figure 1).

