A clinical psychologist specializing in CBT will perform the intervention during the 9-session therapy protocol. Each session will last about 1.5 hours and will be organized as described in Table 1.

First, mindfulness, which has been found effective in individuals with WS, will be integrated into each session [37]. Mindfulness is our innate capacity to pay conscious and full attention to something in the moment. It is often defined as “the awareness that emerges through paying attention on purpose, in the present moment, and nonjudgmentally to the unfolding of experience” [16]. Usually, anxiety therapy is based on mindfulness-based stress reduction. In this protocol, we adapted mindfulness exercises with some exercises used with children [38-40]. The main exercises are mindfulness of the body, of the breath, and of the senses. Mindfulness exercises are integrated into the app so that the participant can repeat them from home on a daily basis. The protocol will target increasing awareness of the emotions present as well as tolerance to emotional sensations. It will also aim to increase cognitive flexibility and will identify and prevent emotional avoidance behaviors as well as exposure.

The intervention will require the daily use of the WillCope app. In addition to allowing daily assessment by the patient, the WillCope app will provide therapy support through relaxation and mindfulness tools. The presence of a single support to allow self-assessments, as well as the realization of mindfulness and relaxation exercises, is facilitating for patients.

**Table 1 table1:** Main stages of therapy.

Stage of therapy				Description
Retrospective				Each session begins with a look back at the past week and a return to the exercises performed at home.

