## Discussion

In this manuscript, we describe the research protocol for evaluating an anxiety therapy program for individuals with WS. WS is a rare genetic disease in which individuals present with intellectual disability of variable intensity but, in general, have good language skills. Most individuals with WS present with anxiety. Because of the rarity of WS, there is a lack of validated studies on the psychotherapy of anxiety in these individuals. Therefore, their anxiety is usually treated with medication, and the side effects are more severe than in the general population. However, some therapies have been found effective in individuals with intellectual disability. Because of their good language skills, such individuals could particularly benefit from psychotherapy.

This manuscript describes the research protocol to test the effectiveness of CBT for anxiety in individuals with WS. This protocol is based on the single-case and multiple baseline research methodology. This methodology is particularly interesting for 2 aspects. First, it is a scientific research method that applies to small samples (as few as 3 people), so it is a particularly interesting methodology for rare diseases. Second, this methodology enables consideration of interindividual variations by observing the results of each individual individually. It enables evaluation of the fluctuations of anxiety in the daily life of individuals. For this protocol, a smartphone app was developed. This app allows daily self-assessment of anxiety by the patients and can be a support mechanism for the therapy protocol. This app can be particularly helpful for a population with an intellectual disability, for whom the appropriation of certain CBT tools may be difficult.

However, this work has some limitations. First, regarding the app, some improvements might be possible. The developed app has not yet been validated from a psychometric point of view. It can only be used to assess the evolution of anxiety for each patient but cannot be used as a diagnostic tool.

In addition, this app makes it possible to store the participant's evaluation data and thus to know when the patient evaluated his or her anxiety, but there are no data to know how the participant used the other tools in the app (the therapy support tools). It would be interesting to integrate a module to know how often the participant uses the app for therapeutic purposes.

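### Follow-up is described as a period after treatment is withdrawn, but participants are invited to keep using the therapy tools, so it can show maintenance after the sessions end and not persistence without treatment

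*Protocol article*

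**What the plan says.** Study Design defines the control condition as the baseline: "we will first obtain repeated measures during the baseline phase (A) when no treatment is provided". Phase B then runs for 9 weeks, and measurement continues "during 3 months after the treatment to ensure that our measures did not return to the baseline level after the treatment has been withdrawn". The same section explains the choice of design: "The multiple baseline design is well-suited for interventions that are irreversible due to learning effects".

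The Follow-up part of Procedures covers the same three months. After the nine sessions, "individuals will be invited to continue to apply tools delivered during the intervention in their daily life", and "They will continue their daily self-assessment for 3 months after the intervention".

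The Intervention section describes the tools as part of the treatment: "The intervention will require the daily use of the WillCope app", and "the WillCope app will provide therapy support through relaxation and mindfulness tools". Table 1 lists a daily relaxation or mindfulness exercise on the app as the home component of therapy. On whether those exercises are done, the Discussion says "there are no data to know how the participant used the other tools in the app".

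**The concern.** Study Design gives follow-up an inferential purpose, which is to show that scores stay away from baseline once treatment is gone. The Follow-up section describes a phase in which the sessions stop and the self-applied part of the programme may go on by invitation. These are different conditions and support different conclusions.

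At stake is how the follow-up results are read. Under the Study Design wording, stable anxiety scores would be reported as an effect that outlasts treatment, although continued self-treatment could also produce them. A drift back towards baseline would be ambiguous too, since it could follow the loss of the sessions or the participant dropping the tools. Durability is clearly of interest to the authors: the Introduction notes that an earlier mindfulness study in Williams syndrome did not evaluate long-term effects.

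**Working it through.** The point rests on no figure, and the plan gives none to reproduce. The check is to set the statements side by side.

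1. **What ends after the ninth session.** The Follow-up section starts the phase when the nine sessions are complete. The contact with the psychologist stops.

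2. **What may continue.** The same section invites participants to go on applying the tools. The section on the app and the Intervention section show that one app holds both the daily questions and the exercises. Self-assessment continues every day for three months, so the app that carries the exercises stays in daily use. Nothing in the article says the exercises are removed, and the invitation implies that they are not.

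3. **Whether the tools count as treatment.** Daily app use is stated as a requirement of the intervention, and the home exercise appears in Table 1 among the stages of therapy. By the article's own description, the tools are a component of what is being tested.

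4. **Whether the two states can be separated afterwards.** The stored backup shows when self-assessments were made. By the Discussion's own account, it does not show use of the therapy tools. Actual use in follow-up may range from none to daily, and the app data will not show where each of the 5 participants falls.

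5. **Where follow-up enters the analysis.** Data Analysis prefers Tau-U partly because it gives baseline-trend-corrected estimates in the treatment and follow-up phases. It also applies the reliable change index, with a threshold of 1.96, to follow-up against baseline for three WHOQOL-BREF dimensions. Both remain valid as descriptions of change from baseline. What they cannot support is attributing that change to an effect that persists without treatment.

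6. **What is not touched.** The three listed Tau-U indices are A-to-A, B-to-B and A-to-B. None uses the follow-up phase, so the comparison that carries the primary outcome does not depend on how follow-up is labelled.

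Steps 1 to 3 show that the withdrawal label does not fit the phase as described. Step 4 shows that the app data cannot repair this later.

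**The case against.** The best defence is that the two sections can be read together. Treatment in Study Design is the 9-week phase B, so withdrawal may mean only that the delivered sessions are over. The programme teaches skills, and the article itself treats such interventions as irreversible. Continued use of the skills is an intended result, since the digital support is meant to empower participants. The anxiety hypothesis concerns change over the course of therapy, and no hypothesis mentions persistence without the tools. The unrecorded tool use is already disclosed as a limitation.

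Much of this stands. Maintenance after the sessions is a legitimate aim, and the defence rightly narrows the point to the wording of one clause and the conclusion drawn from it. It does not remove the conflict. If withdrawal means only the end of sessions, the clause should say so, because beside a baseline defined by the absence of treatment it invites the reader to see both phases as treatment-free. The disclosed limitation is not linked to the purpose given to follow-up.

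A reader might infer more than the documents support:

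- **That participants must continue treatment in follow-up.** They are invited to. The daily exercise requirement is stated for the therapy period, and only self-assessment is set for follow-up.
- **That lasting effect and continued self-treatment are equally likely explanations.** Nothing in the article bears on their relative likelihood.
- **That the efficacy result is undermined.** The A-to-B comparison does not use follow-up data.

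**Conclusion.** The point holds in a limited form. Two sections describe the same three months in ways that do not agree, and the one that sets the purpose of follow-up promises more than the phase can deliver. Follow-up can show maintenance after the therapist-led sessions end, with self-applied tools still available. It cannot show persistence without treatment.

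The limitation applies to every follow-up day for all 5 participants, because no such day is known from the app data to be free of the tools. It cannot be expressed as an amount of bias, and the length of the phase would not measure one. The primary comparison stands.

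The conclusion assumes that the exercises stay accessible during follow-up, as the invitation implies, and that the app data are the only objective trace of their use. The article does not show the content of the 3-month benefit and satisfaction questionnaire, which may ask about tool use. Even if it does, one retrospective answer could not be matched to daily scores.

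**What to change.** Reconcile Study Design with the Follow-up section. In Study Design, replace the clause about treatment being withdrawn with wording such as: after the therapist-led sessions end, with self-directed use of the tools still possible. State that the follow-up conclusion is limited to maintenance under those conditions, and make no claim of persistence without treatment. This corrects a description and changes nothing that participants are asked to do.

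If follow-up data are still being collected, add a yes/no item on tool use to the caregiver's daily questionnaire, which already runs through follow-up, and show the answers beside each participant's follow-up scores. Treat this as description only. Tool use is self-selected and may itself depend on anxiety, so the item would not separate a lasting effect from continued self-treatment. Collection began in September 2019 and findings were projected for 2023, so the item may come too late for some or all participants. The rewording and the limit on the conclusion remain available.

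The wording change is nearly free. Its cost is a more modest durability claim. The optional item adds a small daily burden for the caregiver.
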